**Fig. 1 Fig1:**
[figure not shown]
Rapid Entire Body Assessment (REBA) score sheet (Ahmadi et al. 2015)

The participants’ data are collected at two points in time, namely, at baseline (1 week before the educational program) and 6 months after it. To prevent attrition and bias, the data are collected from all participants and included in the data analysis, regardless of adherence to the study protocol. The participants will also receive a small gift for their participation.

### Sample size

Sample size calculation is based on the study by Mehrparvar et al. (2012) on MP among Iranian instrumentalists [9], wherein the prevalence of MP in music students had been reported about 44% (p1 = 0.44). If it is assumed that the given rate will decrease to 30% (p2 = 0.30) after the El-Poems intervention, a trial consisting of 185 music students per group would have 80% power (*β* = 0.2) at the 5% significance level (*α* = 0.05). To assume a 10% dropout for each group, at least 204 samples in each group will be needed for the El-Poems study. The following formula is accordingly applied to calculate the sample size:$$n=\left\{{\left({Z}_{1-\upalpha /2}+{Z}_{1-\upbeta}\right)}^2\times \left[{p}_1\left(1-{p}_1\right)+{p}_2\left(1-{p}_2\right)\right]\right\}/{\left({p}_1-{p}_2\right)}^2$$

### Randomization

Totally, there are two national music conservatories in Tehran, Iran. Since individual allocation is not possible in a conservatory’s context, the classes at each conservatory are first randomly divided into two matched groups based on the number of students, grade, and gender. Then, the groups are numbered as 1 and 2 and placed in the bowl. A neutral person is next asked to pull out one of the numbers from the bowl. The group number 1 is thus assigned to the intervention group and 2 is given to the controls. The main researcher also supervises the randomization steps. The current RCT protocol is reported in compliance with the Consolidated Standards of Reporting Trials (CONSORT) guidelines. The El-Poems study flowchart is depicted in Fig. 2.

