## Methods

### Trial design

This study is a matched-pair, two-arm, parallel randomized superiority-controlled trial (RCT), which will be conducted at the Tehran Conservatory of Music, Tehran, Iran, in the 2021–2022 school year. The educational intervention is presented through the web-based Student Education Network (with the acronym, SHAD), initiated by the Ministry of Education to pave the way for sustaining the process of education and learning in the country amid the COVID-19 outbreak.

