### Statistical analysis

The data will be analyzed using the SPSS Statistics software package 24.0 (IBM SPSS 24.0 Ink, NY: IBM Corp). All continuous variables will be also assessed for their normal distribution. *T*-test, Mann-Whitney *U* test, and chi-square test will be then utilized to compare the baseline measurements. The descriptive statistics are also reported to investigate the data. To obtain the time period (at baseline and 6-month evaluation, as the test time factor) in which the difference in mean scores within the groups (viz. group factor) originates, the two-way analysis of variance (ANOVA) will be exploited. The test for homogeneity of the data is further employed for the between-participant variables. Since we do not have a variable with more than one pair, confidence interval adjustment is not selected. The Wilcoxon signed-rank test is additionally calculated for the difference in the MP rate between both study groups. Moreover, the effect sizes will be calculated using the partial eta-squared measure (ηp^2^) that gives the idea of how different the participants are. The significance level will be set at *p* < 0.05.

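### Whole classes are allocated but the planned tests treat students as independent, so standard errors are too small and the 5% error rate is not held

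*Protocol article*

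**What the plan says.** The Trial design section labels the study as follows: "This study is a matched-pair, two-arm, parallel randomized superiority-controlled trial (RCT". It does not mention clusters.

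The Randomization section describes a different unit. It rules out allocating individual students and says that "the classes at each conservatory are first randomly divided into two matched groups based on the number of students, grade, and gender". The division is made within each of two conservatories. The arm is then settled by lot: "A neutral person is next asked to pull out one of the numbers from the bowl". No student is randomised individually.

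The Statistical analysis section fixes the tests by name. Baseline measurements are compared with the t-test, Mann-Whitney and chi-square tests. For scores over the two time points, "the two-way analysis of variance (ANOVA) will be exploited", with group and time as factors. The pain rate is compared between groups with a Wilcoxon signed-rank test, and significance is set at 0.05. No class term, conservatory term, matching factor, cluster-robust variance or class-level analysis appears.

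The Sample size section uses the standard formula for two independent proportions (44% against 30%), without an ICC or a design effect.

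**The concern.** The analysis does not follow the randomisation. Students in one class share a grade, a teacher and a conservatory. The intervention itself works partly through social influence and group activity (The El-Poems intervention, Table 1). Classmates' pain and posture scores should therefore be expected to move together.

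A test that counts students as independent leaves out the between-class variance of the arm difference. P-values, and any intervals reported, then look more precise than the design supports. This affects both primary outcomes (presence and intensity of pain) and the secondary outcome, REBA. A result below 0.05 could reflect which classes fell into which arm rather than the teaching.

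**Working it through.** **1. The plan's own figure.** Inputs from the Sample size section: p1 = 0.44, p2 = 0.30, two-sided 5%, 80% power.

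- Printed formula: n = (1.96 + 0.84)² × [0.44 × 0.56 + 0.30 × 0.70] / 0.14² = 182.6, so 183 per group. The pooled-variance version gives 186. The stated 185 lies between them, with power 79.9%.
- Dropout: 183 / 0.9 = 203.3, so 204; 185 × 1.1 = 203.5, so 204; 185 / 0.9 = 205.6, so 206. The stated 204 is reproduced closely enough.

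The figure therefore rests on independent students, with no allowance for classes.

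**2. Effect of clustering.** Class size m and the ICC are not in the document, so both are assumed.

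- Design effect: DE = 1 + (m − 1) × ICC
- True SE / unadjusted SE = √DE
- True two-sided error of a nominal 5% test = 2 × [1 − Φ(1.96 / √DE)]
- Power of a valid cluster-adjusted test: two-proportion power at 185 / DE per group
- Size needed for 80% power: 185 × DE, then divided by 0.9 for dropout

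| m | ICC | DE | SE ratio | True type I error | Adjusted power at 185 | n per group (before / after dropout) |
|---|---|---|---|---|---|---|
| 15 | 0.01 | 1.14 | 1.07 | 6.6% | 75% | 211 / 235 |
| 20 | 0.02 | 1.38 | 1.17 | 9.5% | 66% | 256 / 285 |
| 20 | 0.05 | 1.95 | 1.40 | 16.0% | 51% | 361 / 402 |
| 30 | 0.05 | 2.45 | 1.57 | 21.1% | 43% | 454 / 505 |

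Worked example, m = 20 and ICC = 0.02: DE = 1 + 19 × 0.02 = 1.38; √1.38 = 1.17; 1.96 / 1.17 = 1.67; two-sided error 0.095.

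**3. Check by simulation.** Binary outcomes with a 44% rate in both arms, about 204 students per arm, beta-binomial class rates and 20,000 runs per setting gave these rejection rates for the unadjusted test:

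- m = 15, ICC 0.01: 6.6%
- m = 20, ICC 0.02: 9.7%
- m = 20, ICC 0.05: 16.2%

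These agree with the formula. At a harsher assumption (m = 25, ICC 0.10) the formula gives 28.8% and the simulation 29.2%.

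**The case against.** The mismatch itself is hard to dispute. The case against concerns its size and reach.

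- **Not all five tests matter equally.** The t-test, Mann-Whitney and chi-square tests serve baseline comparisons. The error rate at stake is that of the ANOVA and the pain-rate test. This stands, but those two carry every outcome.
- **The formula describes an unadjusted two-sample comparison.** The Wilcoxon signed-rank test is a paired test, so the percentages are not literally its error rate; its unsuitability for comparing a rate between two separate groups is another fault. A group-by-time contrast also cancels class differences that stay constant, so the relevant ICC is that of change, which may be lower. This stands as a limit on precision. It is one reason to read the lower rows of assumed ICC seriously.
- **Matching works the other way.** Omitting matching factors that predict outcome makes a test conservative. With perfect balance on them, the two errors cancel only if the matching factors explain (m − 1) times the residual between-class variance. As a share of total variance that is 14 × 0.01 = 14% in the mildest case, 19 × 0.02 = 38% in the second, and 29 × 0.05 = 145%, which is impossible, in the last. Some offset is plausible; the plan models neither side and cannot show it.
- **Number of classes.** With 408 students and 15 to 30 per class there would be about 27 down to 14 classes. Fixed effects for conservatory (1 df), six grades (5 df) and gender (1 df) are heavy for that number. The protocol also describes matched groups of classes and does not define class pairs. Both points stand and bear on how the fix is specified.

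An unseen analysis plan does not answer the point, because the article commits to named tests that conflict with its own allocation.

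**Conclusion.** The concern holds. The class is the unit of allocation, and the outcome tests named in the protocol ignore it. Under assumed class sizes of 15 to 30 and an ICC of 0.01 to 0.05, a nominal 5% test runs at about 6.6% to 21%, with standard errors understated by a factor of 1.07 to 1.57. The exact size depends on two quantities that the document does not give, and it shrinks towards nothing as the residual ICC approaches zero or the matching offset grows. The protocol neither claims nor justifies either condition. Because the primary inference is affected, this must be corrected before the analysis.

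**What to change.** 1. Describe the trial as a matched cluster-randomised trial. State the number and size of the classes and exactly how they were matched.
2. Analyse presence of pain with a mixed logistic model or GEE, and NRS and REBA with linear mixed models. Use a class random effect (or class as the GEE cluster) and include conservatory, grade and gender as fixed effects. Use small-sample degrees of freedom or a small-sample variance correction, and keep the coding of grade economical if classes are few.
3. If there are too few classes for this, analyse class-level summaries, within matched pairs where such pairs were in fact formed and otherwise with adjustment for the matching strata.
4. Report the observed ICC for each outcome.
5. Restate power with a design effect based on a justified ICC.

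Items 1 to 4 need only new wording and a different procedure on data already planned. The price is wider intervals. Item 5 may show that 204 per group gives less than 80% power. Since the protocol counts only two national music conservatories in Tehran, a larger sample may not be available there, and the shortfall should then be stated openly.

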### The El-Poems intervention

THE intervention program consists of four sessions, each one lasting for 90 min with a 1-week interval. The program will be accordingly implemented by a trained physical education instructor and a health educator. The educational content of the given program is developed with reference to previous studies [11, 12, 14, 15, 18–23]. The music students in the control group also receive a little information about the hearing health. In addition, there are no concomitant interventions that are prohibited during the trial.

The educational program includes three components of raising awareness, building motivation, and developing skills (Table 1), as explained below:*Raising awareness*: It is comprised of a theoretical session to raise awareness and promote knowledge about the importance of proper posture during the playing along with brief explanations about the anatomy and physiology of the musculoskeletal system as well as the basic body posture in relation to playing a musical instrument, warming-up and cooling-down, stretching, relaxation, instrument-specific biomechanics, and ergonomics.*Building motivation*: This component involves one session, including creating positive attitudes toward paying attention to ergonomic postures during playing and benefits of proper posture behavior, social influence (viz. norms, behavior, and support of others), and self-efficacy expectations (namely, perceived ability to perform posture behaviors).*Developing skills*: It consists of two practical sessions, containing attention to body posture during playing a musical instrument, proper posture while standing, sitting, lifting, and carrying instruments, upper limb position, special stretching exercises, and warming-up before playing.

**Table 1 Tab1:** Content, timeline, components, methods, and responsibilities of the El-Poems study

Content	Components	Methods	Who
Session 1. Promoting in awareness Date: 1–4 December 2021	Improvement of knowledge about importance of proper posture during playing; a brief review of the musculoskeletal system’s anatomy and physiology; to explain about: basic body posture in relation to playing a musical instrument (e.g., standing, sitting, upper limbs, lifting, and carrying position), warming-up and cooling-down, stretching, relaxation, instrument-specific biomechanics, and ergonomics	- Lecture	Main investigator, conservatory health educator
		- Brainstorm, Q & A	

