		- Showing Power Point, - Uploading posters, pamphlets, text, ...	
Session 2. Promoting in motivation Date: 6–9 December 2021	Creating a positive attitude toward paying attention to proper postures during playing and its advantages; social influence beliefs (norms of others, behavior of others, and support of others); and self-efficacy expectations (the perceived ability to perform posture behavior)	- Group discussion	Main investigator, conservatory health educator
		- Modeling	
		- Increase risk perception	
		- Benefits of proper posture	
		- Recording participants’ thoughts and experiences about proper posture	
Sessions 3 and 4. Development of skills Date: 11–23 December 2021	Improvement of participants’ abilities to accomplish proper posture behavior: implementation of paying attention to body posture during playing a musical instrument, having proper posture while standing, sitting, lifting and carrying musical instrument, upper limbs position, and practicing special stretching exercise and warming up before playing	- Direct experience	Main investigator, Conservatory physical education instructor and health educator
		- Vicarious experience	
		- Demonstration, re- demonstration	
		- Verbal persuasion	
		- Corrective feedback	

During four online sessions in total, all music students in the intervention group are encouraged to participate in the discussions and ask their questions.

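### As described, the bowl draw cannot change the allocation: the groups are numbered beforehand and group 1 is always the intervention, so the split and the labelling settle the arms

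*Protocol article*

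**What the plan says.** The Randomization section gives the allocation as a sequence.

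1. Splitting: "the classes at each conservatory are first randomly divided into two matched groups based on the number of students, grade, and gender".
2. Labelling: "the groups are numbered as 1 and 2 and placed in the bowl". Who assigns the numbers, and how, is not said.
3. Drawing: "A neutral person is next asked to pull out one of the numbers from the bowl".
4. Assignment: "The group number 1 is thus assigned to the intervention group and 2 is given to the controls".
5. Oversight: "The main researcher also supervises the randomization steps".

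On delivery, Table 1 gives the persons responsible for sessions 1 and 2 as "Main investigator, conservatory health educator", and for sessions 3 and 4 as "Main investigator, Conservatory physical education instructor and health educator". The running text of the section on the intervention differs: there the programme is "implemented by a trained physical education instructor and a health educator", and the investigator is not named.

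**The concern.** The neutral person's draw is the only step in the sequence that is expressly given to someone with no stake in the result. If the draw has no effect on the arms, that safeguard is lost, and the decision moves back to the labelling, which has no named owner. The supervisor of these steps seems to be a person who also teaches the intervention.

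This matters more here than in many trials. The primary outcomes, presence and intensity of pain, are self-reported, and students know what teaching they receive. Sound allocation is therefore the main protection against a difference between the arms at the start. If someone could choose which group of classes is taught, a later analysis could not fully undo it.

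**Working it through.** No figure in the protocol depends on this point, so there is none to reproduce. The check is a reading of the sequence, an enumeration of the draw, and a count of allocations.

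**Enumeration of the draw.** Inputs: the groups carry their numbers before the draw; number 1 maps to intervention and number 2 to control; no sentence links the drawn number to an arm.

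| Number drawn | Arm of group 1, as written | Arm of group 1, if the drawn group became the intervention |
|---|---|---|
| 1 | intervention | intervention |
| 2 | intervention | control |

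P(group 1 is intervention), as written: 1/2 × 1 + 1/2 × 1 = 1.

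P(group 1 is intervention), if the draw decided: 1/2 × 1 + 1/2 × 0 = 0.5.

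**What then settles the arms.** With an inert draw, two steps remain: the split and the labelling.

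- Split random, labelling random: the allocation is random and the draw is redundant.
- Split random, labelling chosen: the make-up of the two groups is random, but the labeller picks which one is taught.
- Split not random: both the make-up of the groups and the arm could be chosen. The protocol says the split is random, so its text gives no basis for assuming this case.

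**Number of possible allocations.** The protocol does not give the number of classes, so take k matched class pairs as an assumption, and take a random split within pairs as one way to carry out the stated matched division. Splitting k pairs into two unlabelled groups gives 2^(k−1) possibilities. One deciding draw doubles this to 2^(k−1) × 2 = 2^k.

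- k = 4: 8 × 2 = 16
- k = 8: 128 × 2 = 256
- k = 12: 2048 × 2 = 4096

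With k = 8 divided as four pairs at each of the two conservatories and one deciding draw at each, the count is (2^3 × 2)^2 = 256, the same. Independent randomisation within each of k pairs also gives 2^k. So a random split followed by a draw that decides the arm is as rich as randomising pair by pair, whatever k is. The fault lies in the missing link between draw and arm, not in the number of random units.

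**Who supervises and who teaches.** The Randomization section uses the title main researcher; Table 1 uses main investigator and lists that role for all four sessions. That they are the same person is a reasonable inference but is not stated, and the running text on delivery leaves the investigator out.

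**The case against.** The best defence has four parts.

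*The split is already random.* This stands, and it sets the limit on the point. A reader might infer that the allocation is not random at all, that too few random units remain for a design-based test, or that no class pairs are randomised despite the matched-pair label. The documents support none of these. The division of classes is stated to be random and matched on size, grade and gender. Randomising within pairs is one natural way of doing that, and the count above shows that such a split plus one deciding draw loses nothing.

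*The wording is merely loose.* The word thus presents the assignment as following from the draw, and a draw by a neutral person makes little sense unless it decides something. This is plausible as to intent. It does not rescue the text, which numbers the groups before the draw and then gives each number a fixed arm.

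*A journal article condenses.* How the random split is generated may well stand in the full protocol, so its absence here is not held against the plan. The sequence and the label-to-arm rule are different: they are stated, and a fuller document could not make them work without contradicting them.

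*Supervising is not performing.* A neutral person draws, and the identity of supervisor and teacher is inferred. Both are fair. A reader might infer that the investigator steered the arms; nothing in the documents shows that. What remains is an opportunity that the described procedure leaves open.

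**Conclusion.** The point holds in a limited form. Under the procedure as written, the draw has no influence on the arms (probability 1 rather than 0.5 that group 1 is the intervention), so the neutral person's step protects nothing. The split and the labelling determine the allocation, under the oversight of someone who probably also delivers the sessions.

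The exposure is one choice between two groups already matched on size, grade and gender, or one such choice per conservatory if each has its own labelling. It becomes bias only if the labelling is not random and the labeller has reason to prefer one group; the documents do not show that either is so. The conclusion rests on reading the steps in the order given, and, for the conflict of roles, on taking main researcher and main investigator to be the same person. It should be corrected because it concerns the step on which the claim of randomisation rests.

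**What to change.** In the Randomization section:

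- Delete the fixed rule that group 1 is the intervention and group 2 the control. State that the number drawn decides which group receives the intervention, with one draw at each conservatory. Randomising within each matched class pair would be an equivalent alternative.
- Fix the list of classes beforehand, and have the neutral person already planned carry out the random split, the labelling and the draw from that list.
- Remove the main researcher from the supervision of these steps.

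In the section on the intervention, reconcile the running text with Table 1 on whether the main investigator delivers sessions, and say whether this is the same person as the main researcher.

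If allocation has already taken place, the same sentences should report what was actually done: who split and labelled the groups, and whether the drawn number decided the arm.

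The cost is a few reworded sentences and a little more of the neutral person's time. No added participants, data or staff are needed, and the sample size does not change.

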**Fig. 2 Fig2:**
[figure not shown]
The El-Poems study process flow diagram

### Statistical analysis

The data will be analyzed using the SPSS Statistics software package 24.0 (IBM SPSS 24.0 Ink, NY: IBM Corp). All continuous variables will be also assessed for their normal distribution. *T*-test, Mann-Whitney *U* test, and chi-square test will be then utilized to compare the baseline measurements. The descriptive statistics are also reported to investigate the data. To obtain the time period (at baseline and 6-month evaluation, as the test time factor) in which the difference in mean scores within the groups (viz. group factor) originates, the two-way analysis of variance (ANOVA) will be exploited. The test for homogeneity of the data is further employed for the between-participant variables. Since we do not have a variable with more than one pair, confidence interval adjustment is not selected. The Wilcoxon signed-rank test is additionally calculated for the difference in the MP rate between both study groups. Moreover, the effect sizes will be calculated using the partial eta-squared measure (ηp^2^) that gives the idea of how different the participants are. The significance level will be set at *p* < 0.05.

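### The plan has no between-arm analysis of 6-month MP presence that adjusts for the student's own baseline MP, although baseline MP is collected; adjusting would be a nearly free gain in precision

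*Protocol article*

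**What the plan says.** All references are to the protocol article.

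- **Outcome.** Under Outcomes and measures, presence of MP on the Nordic Body Map is one of two primary outcomes. The other is pain intensity.
- **Timing.** The same section says: "The participants’ data are collected at two points in time, namely, at baseline (1 week before the educational program) and 6 months after it".
- **Sizing.** Under Sample size, the trial is powered on MP prevalence alone. It starts at 44% and assumes that "the given rate will decrease to 30% (p2 = 0.30) after the El-Poems intervention". On that basis "a trial consisting of 185 music students per group would have 80% power" "at the 5% significance level". The formula shown is the unadjusted one for two proportions.
- **Allocation.** Under Randomization, classes are allocated, not students. The matching factors are class size, grade and gender. Baseline MP is not among them.
- **Use of baseline.** Under Statistical analysis, a t-test, a Mann-Whitney test and a "chi-square test will be then utilized to compare the baseline measurements". A two-way ANOVA with time and group factors also uses baseline, but it concerns mean scores.
- **MP rate.** The one test named for it is the Wilcoxon signed-rank test, "additionally calculated for the difference in the MP rate between both study groups". No covariate or stratum is attached to it, and the pairs are not defined.

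**The concern.** A student's MP status at entry is likely to predict MP status six months later. The Background section describes MP in this population as often chronic, though it adds that acute pain also occurs. A comparison of 6-month rates that conditions on baseline status removes the part of the outcome variance that baseline explains. The plan collects the variable but names no analysis that uses it in this way.

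The baseline significance tests do not fill the gap. A non-significant result does not remove an imbalance, and a significant one triggers no planned adjustment. At stake is the precision of the arm difference on which the trial was sized.

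**Working it through.** **1. Reproduce the plan's sample size.** Inputs from Sample size: p1 = 0.44, p2 = 0.30, two-sided alpha 0.05, power 80%.

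n = (1.960 + 0.842)² × [0.44 × 0.56 + 0.30 × 0.70] / 0.14² = 7.849 × 0.4564 / 0.0196 = 182.8, so 183 per arm. The pooled-variance version gives 186. The stated 185 lies between them.

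Power at 185 per arm: standard error = √(0.4564/185) = 0.0497, and Φ(0.14/0.0497 − 1.96) = 0.805 (0.799 with pooled variance). The stated 80% is reproduced for an unadjusted comparison of independent students.

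**2. Does any named analysis give a baseline-adjusted arm difference in MP presence?**

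- *Balance tests.* They compare baseline only and estimate no effect at 6 months.
- *Two-way ANOVA.* It is stated for mean scores, not for the binary rate.
- *Signed-rank test, pairs formed across arms.* Baseline MP is not used.
- *Signed-rank test, pairs formed within student.* Baseline MP enters, but the test addresses change within students. Suppose the changes were then compared between arms. With similar variances at the two times, the variance is 2(1 − ρ) times the unadjusted one, against (1 − ρ²) with covariate adjustment. At ρ = 0.5 these are 1.00 and 0.75. Below 0.5 the change comparison is worse than ignoring baseline: at ρ = 0.3 its power is 0.66, against 0.80 unadjusted.

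None of the four does.

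**3. What adjustment would gain.** Let ρ be the correlation between baseline and 6-month MP presence. The documents do not give it, so it is an assumption and is shown as a range. Power = Φ(0.14 / √[0.4564 (1 − ρ²)/185] − 1.96). As a check, 20,000 trials per setting were simulated with 44% MP at baseline, using a Mantel-Haenszel test stratified by baseline MP.

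| Assumed ρ | Power, formula | Power, simulation | Gain over 0.805 (points) |
|---|---|---|---|
| 0.2 | 0.820 | 0.822 | 2 |
| 0.3 | 0.840 | 0.829 | 4 |
| 0.4 | 0.868 | 0.859 | 6 |
| 0.5 | 0.902 | 0.896 | 10 |
| 0.6 | 0.941 | 0.941 | 14 |
| 0.7 | 0.977 | 0.978 | 17 |

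The unadjusted test had simulated power of 0.79 to 0.81 throughout. In a separate simulation at ρ = 0.5 with 184 per arm, type I error was 0.050 unadjusted and 0.048 stratified.

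**4. Effect of class allocation.** The protocol gives neither class size nor intraclass correlation (ICC). Assume 20 students per class and an ICC of 0.02. The design effect is 1 + 19 × 0.02 = 1.38, and the effective size is 185/1.38 = 134 per arm. The same formula then gives Φ(0.14/√(0.4564/134) − 1.96) = 0.67 unadjusted and 0.79 adjusted at ρ = 0.5. The level falls by more than 10 points, while a gain of about 12 points remains.

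**5. Chance imbalance.** With 185 independent students per arm and 44% baseline MP, the baseline difference has a standard deviation of √(2 × 0.44 × 0.56/185) = 5.2 points. At ρ = 0.5 that carries 0.5 × 5.2 = 2.6 points into the 6-month difference. This is the component that the factor (1 − ρ²) removes in step 3, so it must not be added to the power gain.

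**The case against.** Four objections deserve an answer.

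**Baseline MP may already be used.** A reader might infer that baseline MP is only tested for balance and never reaches the MP-rate analysis. The document does not support that. The signed-rank test is a paired test, and the remark in the same section about no variable having more than one pair may point to pairs within student. This objection stands against the stronger reading. It does not rescue the plan, because neither way of pairing yields a baseline-adjusted arm difference.

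**The article is condensed and covariates belong in the SAP.** This would be decisive if the section were silent. It is not: it fixes the use made of baseline measurements and the test for the MP rate. The point concerns those stated choices.

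**No power is lost.** This is correct. The trial was sized for an unadjusted comparison, and that comparison has about 80% power on the plan's inputs. A reader might also infer a fixed loss of about 10 points, but that figure holds only at a correlation near 0.5, which the protocol does not give, and only for independent students. Nor does chance imbalance add a bias: under randomisation it is part of the sampling variance already counted.

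**The correlation may be low.** The Participants section excludes students with musculoskeletal injury or ill health. If that removes those with MP at entry, baseline MP varies little and the gain shrinks. The Sample size section, however, speaks of a 44% rate falling to 30%, which presupposes substantial MP at entry. If few students have it, adjustment gains little but costs almost nothing.

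**Conclusion.** The point holds as a missed gain in efficiency. The Statistical analysis section plans no between-arm comparison of 6-month MP presence that conditions on baseline MP. The baseline variable is collected anyway and is not balanced by the matching.

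Under the plan's own inputs and independent students, the gain runs from about 2 points of power at an assumed correlation of 0.2 to about 17 at 0.7. The protocol gives no basis for choosing a value within that range. Class allocation lowers the absolute levels, and the exclusion criteria may reduce the gain. The conclusion does not depend on any particular correlation, because the data exist and adjustment costs little even when the correlation is small.

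**What to change.** In the Statistical analysis section:

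1. Replace the baseline significance tests with a description of baseline characteristics, including MP presence, by arm.
2. In place of the signed-rank test, make the primary MP-rate analysis a prespecified between-arm model of 6-month MP presence, with arm and the student's own baseline MP presence as terms. The model must account for the allocation of classes.
3. Report the marginal risk difference with its confidence interval, which is on the same scale as the 14-point difference used for sizing.

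The cost is wording, plus slightly more analysis work than comparing raw rates. No new data, visits or students are needed. Because the correlation is unknown, the gain should be kept as a reserve and not used to reduce the sample size.
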